## Methods

### Study design and setting

This study is a parallel-group, superiority trial. All study participants will first undergo protocol-based group CBT [10] for 12 weeks, and within 10 days after the end of the CBT intervention, they will be randomly assigned (1:1 ratio) to either 10 weeks of in-home decluttering or a waitlist. Participants randomized to the waitlist will be offered in-home decluttering at 10 weeks post-randomization (i.e., after the primary endpoint). All participants will be followed up naturalistically 3, 6, and 12 months after the primary endpoint. Figure 1 shows a CONSORT flow diagram [11] of the study design. A SPIRIT checklist [12] can be found in the supplements.

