### Outcome measures

Assessments will be conducted at several time points throughout the trial. All measures and measurement points are shown in Fig. 2; for more details, see supplement 1 (full protocol). Baseline assessment occurs after CBT, and during the first home visit of in-home decluttering or waitlist. Two mid-intervention assessments will be done, one at week 4 and the other at week 7 after randomization. The primary endpoint is 10 weeks after randomization.

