### Sample size calculation and statistical analysis

The power calculation in the current trial is based on individual-level data from a previous study of group CBT for HD with the SI-R as the primary outcome measure, rated at 3 time points [23]. A linear, 2-level mixed effects model (LMM) implemented using the R package powerlmm, version 0.4 (available at https://cran.r-project.org/src/contrib/Archive/powerlmm/) [43] was used to calculate the required sample size. In this model, the standard deviations of the random intercept (4.22), the random slope (2.54), and the residual error (5.68) were imputed. Given 80% power (two-sided alpha test), two groups (in-home decluttering and waitlist), and 4 SI-R observations (baseline, week 4, week 7, post-intervention) per participant, we estimated that a total of 80 participants would be needed to detect a slope difference between the two groups of 8 points on the SI-R at the primary endpoint. For the other primary outcome measure, the blind assessor-rated CIR, data from the same study was used. In that study, there were only data from two measurement points, and therefore, an ANCOVA was used to calculate power, adjusting for pre-treatment scores. Given 80% power (two-sided alpha test), two groups (in-home decluttering and waitlist), and 4 CIR observations (baseline, week 4, week 7, post-intervention) per participant, the estimate is that a total of 58 participants would be needed to detect a slope difference between the two groups of 1 point on the CIR at the primary endpoint.

To compensate for up to 15% missing data throughout the trial, we will recruit a total of 90 participants who will be randomized to one of two trial arms. However, due to the risk of dropouts before randomization, during or immediately after CBT, we plan to recruit patients to CBT until we have randomized 90 participants.

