All data will be analyzed according to intention-to-treat principles with mixed effects models. The mixed effect regression model will include fixed effects of time, trial arm (intervention vs. waitlist), and an interaction effect of time by trial arm, as well as a random intercept to account for individual differences. Ordinal variables (such as the CGI-I and the CGI-S) will be analyzed with ordinal regression and binary data (e.g., remitter status) with logistic regression. The chi-square tests will be used to check whether the blinded assessor’s guesses on trial arm allocation are better than chance. The selected statistical model of mixed effect regressions can handle missing data, if more than 15% of data is missing an appropriate imputation method will be applied. Potential selection bias due to missing data will be assessed by comparing data from enrollment and baseline from participants with and without missing data on the primary outcomes using linear regression and by conducting sensitivity analysis. The statistician that will perform the data analyses will be independent from the research group and blind to group allocation.

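### The SI-R sample size assumes slopes that vary between participants, but the stated analysis model has only a random intercept, so a linear time-by-arm test would be anti-conservative under the plan's own variance components

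*Protocol article*

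**What the plan says.** Both statements stand in the protocol article, under Sample size calculation and statistical analysis.

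- **Power model for the SI-R.** It is a two-level linear mixed model in which "the standard deviations of the random intercept (4.22), the random slope (2.54), and the residual error (5.68) were imputed". The inputs come from an earlier study of group CBT "with the SI-R as the primary outcome measure, rated at 3 time points". The design is set out as "Given 80% power (two-sided alpha test), two groups (in-home decluttering and waitlist), and 4 SI-R observations (baseline, week 4, week 7, post-intervention) per participant", with the result that "a total of 80 participants would be needed to detect a slope difference between the two groups of 8 points on the SI-R".
- **Analysis model.** It has fixed effects of time and trial arm, "an interaction effect of time by trial arm, as well as a random intercept to account for individual differences". No random slope, other covariance structure or robust standard error is named. The text does not say whether time is linear or categorical.

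The article gives neither the time unit of the slope SD nor the numerical significance level. For the CIR it gives no variance components: the earlier data had two measurement points, and power came from an ANCOVA.

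**The concern.** The treatment effect is carried by the time-by-arm interaction. If participants differ in their rate of change, the standard error of a between-arm difference in slopes has to include that variation. A random-intercept model treats all pairs of visits as equally correlated. It puts the slope variation into the residual and then averages it over visits as if it were independent noise. The interaction's standard error comes out too small, the test rejects too often and the confidence interval is too narrow.

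The plan itself assumes such variation when it sizes the trial and then leaves it out of the model it describes for analysis. Two things are at stake: the error rate of a superiority claim on the SI-R, and the meaning of the stated 80% power, which belongs to a different model from the one described.

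**Working it through.** **Inputs**

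- SI-R SDs: intercept 4.22, slope 2.54, residual 5.68 (sample size section). Squares used: 2.54² = 6.4516 and 5.68² = 32.2624. In balanced data the intercept drops out of the slope comparison.
- Four observations per participant; effect of 8 points at the endpoint; 80% power; N = 80 (same section).
- 45 per arm: "To compensate for up to 15% missing data throughout the trial, we will recruit a total of 90 participants", with 1:1 allocation.
- Visits at baseline, weeks 4, 7 and 10: "Two mid-intervention assessments will be done, one at week 4 and the other at week 7 after randomization".
- Assumptions: two-sided alpha of 5%, and a time code T for the last visit.

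**Step 1: reproduce N = 80**

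Variance of one participant's slope = 6.4516 + 32.2624/SSx, where SSx is the sum of squared deviations of the visit times. Slope difference = 8/T. Number per arm = 2 × (1.960 + 0.842)² × variance / (8/T)².

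- T = 4, equal spacing: SSx = 8.89; variance = 6.4516 + 3.6295 = 10.08; slope difference 2. Number per arm = 2 × 7.849 × 10.08 / 4 = 39.6, so 40 per arm and **N = 80**. A t-based version gives 82.
- Times 0, 1, 2, 3: SSx = 5; variance = 6.4516 + 6.4525 = 12.90; slope difference 2.667. Number per arm = 2 × 7.849 × 12.90 / 7.111 = 28.5, so 29 per arm and N = 58. The t-based version gives 60.

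The stated 80 is therefore reproduced with T = 4 and not with visits coded 0 to 3.

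**Step 2: linear slope test from a random-intercept model**

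That model's residual variance tends to 32.2624 + 6.4516 × SSx/3, and its slope variance is this residual divided by SSx.

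| | Times 0–3 | T = 4 |
|---|---|---|
| True slope variance | 12.90 | 10.08 |
| Model residual | 32.26 + 10.75 = 43.02 | 32.26 + 19.12 = 51.38 |
| Model slope variance | 43.02/5 = 8.60 | 51.38/8.89 = 5.78 |
| Ratio, true to model | 1.50 | 1.74 |
| Effective critical value | 1.96/√1.50 = 1.60 | 1.96/√1.74 = 1.48 |
| Type I error | 10.9% | 13.8% |
| Coverage of nominal 95% interval | 89% | 86% |
| Interval too narrow by | 18% | 24% |

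Actual spacing at weeks 0/4/7/10 gives 10.9% and 13.7%. Simulating 20,000 null trials with 45 per arm gives 11.2% and 13.7% (equal spacing). REML fits in 400 null trials give 10.0% and 13.75%. With slope heterogeneity taken into account, simulated type I error is 4.7 to 5.0%.

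**Step 3: categorical time**

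- Change from baseline to week 10. True variance = 2 × 32.2624 + 6.4516 × T²; model variance = 2 × residual from Step 2. For T = 3: 122.6 against 86.0, type I error 10.1%. For T = 4: 167.8 against 102.8, type I error 12.5%.
- Joint 3-df interaction test, simulated: 5.4% (T = 3) and 6.1% (T = 4).

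**Step 4: sensitivity**

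Codings that do not reproduce N = 80, linear slope test:

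| Coding | Type I error | N for 80% power |
|---|---|---|
| T = 1 | 5.8% | 32–34 |
| T = 2 | 8.1% | 42–44 |
| Months | 8.9% | 46–48 |
| Weeks | 21.5–22.2% | 286–348 |

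Half the slope SD (1.27, square 1.613):

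- Times 0–3: true 8.07, model 6.99, ratio 1.15, type I error 6.8%.
- T = 4: true 5.24, model 4.17, ratio 1.26, type I error 8.1%.

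**The case against.** **The size is conditional.** The time unit of the 2.54 is not printed. T = 4 is used because it returns 80, no section states it, and other unprinted inputs could also lead to 80. The 11% figure uses a coding that needs only 58 to 60 participants. This stands: the percentages illustrate the plan's assumptions and are not a known property of the trial. The direction does not depend on the coding, since every one tried inflates the linear slope test.

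**The slope SD comes from another setting.** It was estimated in a group CBT study. Here all participants have finished CBT and one arm waits, so heterogeneity may be smaller. This also stands, and the halved-SD result shows its effect.

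**The time-by-arm term may mean a joint test.** If time is categorical and the interaction is tested on 3 df, the error is close to nominal. This is correct. However, the power section frames the effect as a slope difference at the primary endpoint, which points to a linear slope or a week-10 contrast, and both of those are inflated.

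**The article is condensed.** It refers to a full protocol in the supplement, which is not at hand, and it never says that the random intercept is the only random effect. A fuller document may add the slope. The point remains because the article does state a random part, and that part disagrees with the power model in the same section.

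**A broader reading about both outcomes.** A reader might infer that both primary outcomes are tested at 11 to 14%. The article does not support this, because it gives no CIR variance components from which slope variation could be calculated.

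**Conclusion.** The inconsistency is real and should be corrected. The model used to size the SI-R comparison contains a random slope, and the analysis model as stated does not. Taking the plan's SDs at face value with a two-sided 5% level, the random-intercept-only test of the linear slope difference has a type I error of about 14% under the coding that matches N = 80 and about 11% with visits coded 0 to 3. The categorical week-10 contrast has about 10 to 12.5%.

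The documents do not support an unconditional statement that the trial's primary test runs at 11 to 14%. That range depends on an assumed time unit, on an SD carried over from an earlier study and on how time enters the model. For the CIR the mechanism applies if slopes vary, but no figure can be given.

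**What to change.** In the analysis paragraph, specify for the primary analyses a random intercept and a random slope for time, as in the power calculation. If time is to be categorical, specify an unstructured covariance over the four visits instead. State which of the two applies, and settle it before unblinding.

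This takes about one sentence. N = 80 is unchanged, because the power model already contains the slope. The printed SI-R standard errors would be about 22 to 32% larger than those of the random-intercept model under the plan's values (√1.50 = 1.22 and √1.74 = 1.32). That is the price of a correct error rate. The richer model also carries some risk of non-convergence.

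### The 15% imputation trigger should go: it adds nothing for SI-R and CIR, and may leave responder, remitter and CGI analyses unprotected below it

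*Protocol article*

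**What the plan says.** All of this is in the protocol article, section Sample size calculation and statistical analysis, unless noted.

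- General principle: "All data will be analyzed according to intention-to-treat principles with mixed effects models".
- CGI-S and CGI-I, as ordinal variables, "will be analyzed with ordinal regression and binary data (e.g., remitter status) with logistic regression".
- Missing data: "The selected statistical model of mixed effect regressions can handle missing data", followed in the same sentence by the rule that "if more than 15% of data is missing an appropriate imputation method will be applied". What the 15% is a percentage of (participants, visits, or values of one outcome) is not stated.
- The same figure appears in the sample size paragraph: "To compensate for up to 15% missing data throughout the trial", 90 are to be randomized.
- Checks not tied to the 15% line: enrollment and baseline data are compared between "participants with and without missing data on the primary outcomes using linear regression and by conducting sensitivity analysis".
- Under Secondary outcome measures, a responder has an SI-R change of at least 14 points, and a remitter is a responder with an SI-R total below 42. Both are therefore derived from the SI-R. Under Cost-effectiveness analysis, both statuses at the primary endpoint serve as health outcomes.

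**The concern.** This is a stated decision rule, so the question is whether it is a sound one and not whether detail is absent. It has two weaknesses.

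First, it does not follow from its own reason. If the mixed model copes with missing SI-R and CIR values, that is because missingness is assumed to depend only on observed data. The assumption is no safer at 14% than at 16%. Above the line the rule adds an imputation step that gains nothing under that assumption, and whether the step is taken depends on a count known only once the data are in.

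Second, the reason does not extend to an ordinary logistic or ordinal regression of a week-10 result. Such a model uses only participants who have the result. If that is what is meant, nothing is planned for the others when the trigger is not met. Drop-out could well differ between arms, since one arm has ten weekly home visits and the other is waiting for them. A distorted responder or remitter difference would also pass into the cost-effectiveness results.

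**Working it through.** The article derives no figure for the trigger, so there is none to reproduce. Three checks follow.

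**1. How sharp the line is.** Assume that the rule counts participants. With N = 90, 13/90 = 14.4% means no imputation and 14/90 = 15.6% means imputation, so one person decides. The chance that it fires is P(X ≥ 14), with X binomial (90, p):

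| True missing rate p | P(trigger fires) |
|---|---|
| 8% | 0.01 |
| 10% | 0.06 |
| 12% | 0.19 |
| 15% | 0.49 |
| 18% | 0.77 |

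**2. Which outcomes the stated reason covers.**

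| Outcome | Model named | Does the mixed-model reason apply? |
|---|---|---|
| SI-R, CIR (primary) | Mixed model, four visits | Yes, under missing-at-random, at any rate |
| Responder, remitter | Logistic regression | Not if single-time-point |
| CGI-S, CGI-I | Ordinal regression | Not if single-time-point |

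The single-time-point reading is natural because responder and remitter status are defined by an SI-R change, CGI-I rates improvement after treatment, and logistic and ordinal regression are named apart from the mixed model. The article does not state it.

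**3. Possible bias below the trigger, if those analyses use only participants with a week-10 value.**

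Inputs from the article: residual SD 5.68, random slope SD 2.54, an 8-point SI-R difference, and the 14-point responder threshold.

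Assumptions not in the article: the slope SD is per visit interval (time coded 0 to 3); mean SI-R change from the post-CBT baseline is −10 (decluttering) and −2 (waitlist); responder change is counted from that baseline; the log-odds of a missing week-10 value rise by k for each SI-R point less improvement at week 7; and overall missingness is 14%.

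True responder rates:
- SD of change = √(3² × 2.54² + 2 × 5.68²) = √(58.1 + 64.5) = 11.07.
- Decluttering: Φ((−14 + 10)/11.07) = Φ(−0.361) = 35.9%.
- Waitlist: Φ((−14 + 2)/11.07) = Φ(−1.084) = 13.9%.
- True difference: 22.0 points.

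The responder rate among those observed is Σ r(1 − π)/Σ(1 − π), where r is responder status and π the drop-out probability. It was simulated with 1,000,000 participants per arm, with drop-out calibrated to the rates shown. Entries are the responder difference in points, with relative error against 22.0:

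| Missing, decluttering / waitlist | k = 0.05 | k = 0.10 | k = 0.15 |
|---|---|---|---|
| 20% / 8% | 23.8 (+8%) | 25.2 (+14%) | 26.2 (+19%) |
| 14% / 14% | 22.7 (+3%) | 23.4 (+6%) | 23.9 (+8%) |
| 8% / 20% | 21.7 (−2%) | 21.5 (−2%) | 21.5 (−2%) |

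For scale, the standard error of the difference at 45 per arm is √(0.359 × 0.641/45 + 0.139 × 0.861/45) = 8.8 points. The 3.2-point bias in the middle column of the first row (25.2 − 22.0) is about 0.4 of a standard error.

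A cruder extreme makes every missing participant a non-remitter, with assumed remission of 40% and 20%. The observed difference is 0.40/(1 − m₁) − 0.20/(1 − m₂), where m₁ and m₂ are the missing fractions in the decluttering and waitlist arms. Against a true 0.20 it gives 0.233 (14%/14%), 0.283 (20%/8%) and 0.185 (8%/20%). Imputation under missing-at-random would not fully repair that case; it belongs to the sensitivity analysis.

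**The case against.** Several stronger readings are tempting, and the article does not support them.

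- **That binary and ordinal outcomes are analysed on complete cases.** The article never says so. Its opening sentence, "All data will be analyzed according to intention-to-treat principles with mixed effects models", leaves room for mixed logistic or ordinal models. The form of these models may be set out in the full protocol or the SAP, neither of which is shown.
- **That the plan contradicts intention-to-treat.** Not for the primary outcomes. A likelihood mixed model over four visits uses all observed data from randomized participants and needs no imputation to be consistent with that principle.
- **That use of imputation is a coin toss.** The sample size paragraph gives 15% as a ceiling ("To compensate for up to 15% missing data throughout the trial"), not an expected rate. The probability of 0.49 holds only at a true rate of exactly 15% with participants counted; at 10% it is 0.06.
- **That the primary model is swapped above the line.** The article says that imputation will be applied, and imputed data can feed the same mixed model. The threshold is fixed in advance and the statistician is independent and blind to allocation, which limits any choice driven by the arm results.
- **That nothing guards against missing-data bias below the line.** The comparison of participants with and without missing primary outcomes and the sensitivity analysis are planned whatever the amount missing.

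The bias figures also rest on an assumed drop-out pattern whose direction is not established, and they are small beside the sampling error. All of this stands, and it limits the point to secondary outcomes. It does not rescue the rule itself, which has no benefit for SI-R and CIR and rests on a reason that does not reach ordinary logistic or ordinal regression. The planned checks help to diagnose bias but do not supply a responder, remitter or CGI estimate that includes the missing participants.

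**Conclusion.** The 15% trigger is a poor criterion. For SI-R and CIR it is unnecessary, given missing-at-random and an adequate mixed model, and its only effect is to make the analysis depend on how much is missing. For responder, remitter and CGI outcomes it may leave participants without a week-10 value out when the trigger is not met. This rests on the natural but unstated reading that these are single-time-point models.

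On that reading, with 14% missing and the assumptions above, the responder difference ranges from a slight understatement (about 2%) when the waitlist loses more, through 3% to 8% overstatement with equal loss, to 8% to 19% overstatement when decluttering loses more.

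Severity is minor to moderate. It is limited to secondary outcomes and the cost-effectiveness analyses that use responder and remitter status. A reader should not infer that the primary SI-R and CIR analyses are invalid or depart from intention-to-treat.

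**What to change.** Delete the 15% trigger and fix one approach per outcome type, applied at any missing rate:

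- **SI-R and CIR:** the likelihood-based mixed model remains the primary analysis whatever the amount missing.
- **Responder and remitter status:** multiple imputation of the SI-R by arm, using the available week 1, 4 and 7 scores, with both statuses derived from the imputed week-10 score. The same results feed the cost-effectiveness analyses.
- **CGI-S and CGI-I:** multiple imputation by arm, using the earlier scores available.

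The form of the sensitivity analysis already planned can be left to the SAP.

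The cost is a few lines of analysis text and some extra programming. No new data, visits or participants are needed.

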### Cost-effectiveness analysis

In the cost-effectiveness analysis, the costs and health outcomes of the participants in the in-home decluttering group will be calculated and compared to the same costs of the individuals randomized to the waitlist. We will first estimate the direct costs from a treatment provider perspective (e.g., resource use associated with home visits). We will then also include indirect costs, which will widen the scope to a societal perspective (e.g., sick leave or work absenteeism). We will perform both cost-effectiveness and cost-utility analyses. In the cost-effectiveness analyses, overall hoarding symptoms, responder and remitter status, and level of clutter, measured with the SI-R and the CIR, respectively, at the primary endpoint (10 weeks post-randomization) will be used as the health outcome. In the cost-utility analysis, the outcome will be the quality-adjusted life years (QALYs), according to international standards for cost-effectiveness analyses [44]. QALYs will be calculated using the area under the curve method. Costs will be estimated by appropriate regression analyses testing alternative link functions and distributions. Non-parametric bootstrapping with 1000 iterations will be carried out, pairing up differences in costs with differences in outcomes. As a global cost-effectiveness estimate, a visual presentation of cost-effectiveness planes will be presented. The timeframe for the cost-effectiveness analyses will be from baseline to the primary endpoint.

### Quality control

This study was preregistered (ClinicalTrials.gov reference number NCT04712474) prior to the inclusion of the first participant. External monitoring will ensure the good quality of the study procedures. The Karolinska Trial Alliance will monitor random samples of 15% of the study participants, focusing on informed consent forms, identification log, journal entry of consent forms, inclusion/exclusion criteria, primary outcome measures at the primary endpoint (i.e., SI-R and CIR), and serious adverse events. The study will also follow local regulations for data management and protection, the Swedish law, and the General Data Protection Regulation (GDPR).

